# PROTOCOL SUMMARY

## Synopsis

| **Title:** | Skills to Enhance Positivity in Adolescents at Risk for Suicide |
| --- | --- |
| **Grant Number:** | MH123556-01A1 |
| **Study Description:** | The purpose of this study is to examine the effectiveness of the Skills to Enhance Positivity (STEP) intervention in reducing suicidal behaviors in adolescents who have been admitted to an inpatient psychiatric unit due to suicide risk. |
| **Objectives:** | Primary Objective: Examine the effectiveness of STEP in reducing suicidal events (suicide attempt or emergency intervention to intercede attempt), active SI (with intent or plan), and depression at 6-month follow-up (primary endpoint outcomes) and suicidal events at 12-month follow-up (distal, endpoint outcome).  Secondary Objective: Examine engagement of the hypothesized mechanisms (attention to positive and negative affect) at the 3- and 6-month follow-up.  Tertiary Objective: Examine whether hypothesized mechanisms mediate reduction of suicidal events and ideation. |
| **Endpoints:** | Primary Endpoint: Suicidal events, active suicidal ideation, and depression at 6 month follow-up.  Distal Primary Endpoint: Suicidal events at 12 month follow-up.  Secondary Endpoint: Attention to Positive Affect and Negative Affect at 6 month follow-up. |
| **Study Population:** | Adolescents, regardless of sex, gender, race, and ethnicity, between the ages of 12-18, who have been hospitalized due to suicide risk (i.e., a suicide attempt or suicidal ideation) will be recruited for study participation from three adolescent units at Boston Children’s Hospital (Boston, MA), Butler Hospital (Providence, RI), & Bradley Hospital (Providence, RI). Target recruitment is 216. |
|  |  |
| **Phase or Stage:** | Phase III |
| **Description of Sites/Facilities Enrolling Participants:** | Three sites, all in the United States, will be enrolling participants: 1) the adolescent inpatient unit at Boston Children’s Hospital; 2) the adolescent unit of Butler Hospital; and 3) the adolescent inpatient unit at Bradley Hospital |

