# OBJECTIVES AND ENDPOINTS

| OBJECTIVES | ENDPOINTS | JUSTIFICATION FOR ENDPOINTS | PUTATIVE MECHANISMS OF ACTION |
| --- | --- | --- | --- |
| Primary |  |  |  |
| To examine the effectiveness of STEP in reducing suicidal events (suicide attempt or emergency intervention to intercede attempt, i.e. ED evaluation or psychiatric hospitalization), active suicidal ideation (with intent or plan), and depression, compared to ETAU. | Suicidal events and active suicidal ideation as assessed by the Columbia-Suicide Severity Rating Scale (C-SSRS) interview, and depression as assessed by the Beck Depression Inventory (BDI-II) at 6 month follow-up (primary endpoint) and suicidal events at 12 month follow-up (secondary endpoint) | Six-month follow-up is selected as the primary end-point time as numerous studies have shown this to be a particularly high-risk time for repeat suicidal behaviors. Twelve months allow us to assess the long-term effectiveness. | NA |
| Secondary |  |  |  |
| To examine engagement of the hypothesized mechanisms of positive affect (PA) and negative affect (NA). | Attention to PA and NA as assessed by implicit cognitive tasks and self-report forms (See 1.3) at 3 month follow-up (primary) and 6 month follow-up (secondary) endpoint. | PA and NA are hypothesized to be causal mechanisms. Thus these assessments will see if we engaged our treatment target of PA and NA. | PA and NA are hypothesized to be causal mechanisms. |
| Tertiary/Exploratory |  |  |  |
| To examine whether hypothesized mechanisms mediate reduction of suicidal events and ideation. | Attention to PA and NA as assessed by implicit cognitive tasks and self-report forms (See 1.3) at 3 month follow-up (primary) and 6 month follow-up (secondary) endpoint. | The PA and NA assessments, using both implicit and subjective assessments, will be examined as mediators. Specifically, PA and NA at 3 month f/u is hypothesized to mediate the relationship between study intervention and clinical outcomes at the 6 month f/u; and PA and NA at 6 month f/u is hypothesized to mediate the relationship between study intervention and clinical outcomes at the 12 month f/u. | PA and NA will be examined as mediators. |

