# STUDY ASSESSMENTS AND PROCEDURES

## Endpoint and Other Non-Safety Assessments

Please refer to Section 1.3, Schedule of Activities to see list of assessments, assessment modality, and timetable of specific administrations. Of note, guardians will be mainly reporting on adolescent thoughts, feelings, and behaviors for the assessment areas described below.

Demographics and Background Variables. Routine demographic variables will be collected. We will ask questions from the overview of the *Kiddie Schedule for Affective Disorders and Schizophrenia – Present and Lifetime version (KSADS-PL*)(52) to assess for current living situation, legal involvement, history of abuse, family psychiatric history, treatment history and payor information. Self-report forms will be used to ask about sexual and gender identity.

Suicidal Events. Suicidal events (operationalized as a composite score of suicide attempts and inpatient hospital/ED admissions)(42) will be assessed with the *Columbia-Suicide Severity Rating Scale* (50) and the *Child and Adolescent Services Assessment* (53). The C-SSRS assesses the range of suicidal behavior including preparatory acts, aborted attempt and interrupted attempt, and passive and active SI, as well as intensity of ideation. At f/u, suicidality since the last assessment and in the prior week will be assessed. The CASA is a semi-structured interview that obtains information about service use across multiple sectors (e.g., juvenile justices, schools). Adequate reliability has been demonstrated for this measure (ICCs=.74-.76)(53). Interviews will be administered at baseline, 3-, 6-, and 12-months f/u, with the 6-month follow-up as our primary outcome (Ho1A). The CASA will be used to systematically assess ED evaluations and psychiatric hospitalizations.

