# STATISTICAL CONSIDERATIONS

**Data Analyses.** In this section, we describe aim by aim the proposed method of data analysis and sample size considerations. **Scientific rigor** is enhanced and maintained by: 1) randomization procedures, 2) having assessment staff blind to condition, 3) multiple modalities of assessment, 4) comprehensive retention procedures, 5) preliminary analyses, 6) missing data procedures, and 7) data analytic strategies that are consistent with best practices for the analysis of randomized clinical trials as embodied in the Consolidated Standards of Reporting Trials (CONSORT) statement (75)**.** Additionally, relevant biological variables, specifically sex, are considered in the experimental design. We do not have a priori hypotheses regarding sex differences in the effect of STEP on our study outcomes. Accordingly, and in agreement with NIH guidance on this topic our plan is to separately tabulate results by sex but test our main hypotheses in a sample with both sexes combined (<http://orwh.od.nih.gov/sexinscience/overview/pdf/NOT-OD-15-102_Guidance.pdf>). Finally, by collecting implementation outcome data, we will be able to identify and develop implementation strategies to encourage greater uptake and adoption of STEP in a future R01 implementation trial. As all our hypotheses are pre-specified, no adjustment for multiplicity will be used.

[figure not shown]
Our randomization procedures include stratification on important predictors of the main outcome variable and are automated and protected from inadvertently revealing treatment assignment order to staff. This will help ensure the blinding of assessment staff to treatment condition. Our plan for how missing data will be

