***Sample size and statistical power considerations:*** We determined minimal detectable effect sizes using Monte Carlo methods. This involved generating 1,001 simulated data sets representing our hypothesized effects, and our assumptions of a 10% loss by 3M and another 10% loss by 6M follow-up. We assumed repeated measures of depressive symptoms and the propensity to active suicidal ideation and suicidal events were all correlated at *r* = .5. Across the simulated data sets, we compute power as the proportion of replicates returning a significant effect in the hypothesized direction. Results of these models are summarized in Table 3, above. We summarize effects in terms of Cohen’s effect size statistics for clear expression of the minimum detectable effects. For H1A, H1B, and H1C, we will have sufficient power to detect small-to-medium effect sizes (.46, .31, .35, respectively).

**Aim 1D:** *Examine the effectiveness of STEP in reducing suicidal events at the 12-month f/u.* We hypothesize that those randomized to STEP, compared to ETAU, will have lower rates of suicidal events at the 12-month, long term f/u. This hypothesis will be tested to evaluate the durability of STEP effects over long-term follow-up. We expect to see the full effect of STEP at the 6M follow-up. This hypothesis will be evaluated with logistic regression, and not as part of the repeated measures analysis specified in H1A. If the effect continues through 12M, we will have 80% power to detect a difference in event rates of 38% ETAU and 17% STEP at the 12M follow-up.

In secondary analyses, the within-person frequency of suicidal events and suicidal ideation will be analyzed. These analyses will use (zero inflated) negative binomial regression models to account for the anticipated extreme skew of these outcomes.

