***Sample size and statistical power considerations***. The power to test the difference between two proportions, .17 and .38, is significantly different from zero can be found from POWER = F(sqrt(((n*(p1-p2)^2)/(p0*(1-p0)))/2) – F’(1-(a/2))), where F is the cumulative normal density function and F’ is the normal quantile function, a is the desired type-I error level, n is the per-group sample size and p1 and p2 are the target proportions. H1A and H1D have similar minimum detectable effect sizes because we use a conservative estimate of the within-person correlation of propensity to suicide for aims H1A-H1C. We conservatively use 162 as our sample size for these calculations but we expect to have a larger sample with suicidal event data because these data can be drawn from the electronic health record in addition to participant self-report.

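### Pre-specification is given as the reason for no multiplicity adjustment, but it does not control familywise error across three separately tested 6-month primary endpoints with no success rule

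*Protocol*

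**What the plan says.** The opening paragraph of Section 9 settles multiplicity in one sentence: "As all our hypotheses are pre-specified, no adjustment for multiplicity will be used". The same section says that every aspect of the analysis plan is pre-specified.

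The Synopsis lists three outcomes under one heading: "Primary Endpoint: Suicidal events, active suicidal ideation, and depression at 6 month follow-up". It then adds a fourth: "Distal Primary Endpoint: Suicidal events at 12 month follow-up". The table in Section 3 describes the fourth as "suicidal events at 12 month follow-up (secondary endpoint". Overall Design in Section 4 also calls the 12-month endpoint secondary, and there extends it to active ideation and depression.

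Under Aim 1, Section 9 states H1A (suicidal events), H1B (active suicidal ideation), H1C (depression) and H1D (suicidal events at 12 months) as separate hypotheses, each with its own model. The protocol gives no testing order, no split of alpha and no requirement that all endpoints succeed.

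Two members of the family are not fully fixed. Section 9 allows H1B to be analysed as a worst-week binary outcome or as the proportion of weeks with active ideation. Section 8.1 administers the BDI-II to both adolescent and parent, and H1C does not say which report is tested.

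**The concern.** Fixing hypotheses in advance stops the analyst from choosing them after seeing the data. It does nothing to the probability that, among several true null hypotheses, at least one crosses the threshold. With several primary endpoints and no rule for what counts as a positive trial, a significant result on any one could be reported as a positive primary endpoint.

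This could matter in practice. The Synopsis gives the trial's purpose as reducing suicidal behaviors. Section 9 gives suicidal events the largest minimum detectable effect of the three (.46, against .31 for H1B and .35 for H1C). A null result on suicidal events beside a nominally significant result on depression is therefore a realistic outcome, and the protocol does not say how it would be read.

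The sentence is a decision taken in the protocol, not a detail left to a later analysis plan.

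**Working it through.** **Inputs.** Three 6-month primary endpoints (Synopsis), and a fourth if the 12-month endpoint is counted. 108 per arm (216 randomized 1:1), 10% loss by 3 months and another 10% by 6 months, repeated-measures correlation .5, and a detectable effect of .35 for H1C (Section 9). For H1D, 38% vs 17% and 81 per arm (Section 9).

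**Significance level.** The text gives no number. It says only "a is the desired type-I error level", and the formula is two-sided: "F’(1-(a/2))), where F is the cumulative normal density function". Two-sided 5% is therefore an assumption, checked against the plan's own figures in two ways.

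1. *H1D.* The plan states: "we will have 80% power to detect a difference in event rates of 38% ETAU and 17% STEP at the 12M follow-up". The printed formula does not define p0; taking it as the mean rate .275, power = F(sqrt(81 × .21² / (.275 × .725) / 2) − 1.96) = F(2.993 − 1.96) = 84.9%. With a continuity correction, power = F((.21 − 1/81 − 1.96 × .0702) / .0682) = F(.88) = 81.1%, close to the stated 80%.
2. *H1C.* Expected n per arm is 97.2 at 3 months and 86.4 at 6 months. The variance of the two-visit mean difference is 2 × .25 × (1/97.2 + 1/86.4 + 2 × .5/97.2) = .01608, so the standard error is .1268. At 80% power the detectable effect is (1.960 + .842) × .1268 = .355, against .35 stated. At .05/3 it would be (2.394 + .842) × .1268 = .41.

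The stated figures fit an unadjusted two-sided 5%.

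**Familywise error.** With all nulls true and k independent tests, the chance of at least one significant result is 1 − .95^k in either direction and 1 − .975^k in favour of STEP. For k = 3 these are 14.3% and 7.3%; for k = 4, 18.5% and 9.6%. Correlated cases come from 2,000,000 multivariate normal draws. The protocol does not clearly give a correlation between the endpoints' test statistics, so a range is shown.

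| Tests | Counted | r = 0 | r = .5 | r = .9 |
|---|---|---|---|---|
| 3 | either direction | 14.3% | 12.5% | 8.4% |
| 3 | favouring STEP | 7.3% | 6.3% | 4.2% |
| 4 | either direction | 18.5% | 15.6% | 9.4% |
| 4 | favouring STEP | 9.6% | 7.8% | 4.7% |

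For four tests with r = .5 throughout except .8 between the two suicidal-event tests, the results are 14.7% and 7.4%. A single test gives 5% and 2.5%.

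**What adjustment would cost.** A test with exactly 80% power at 5% has 65.8% at .05/3, which is the floor for Holm with three endpoints.

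In a fixed sequence H1A keeps full alpha. The pilot effect reported in the Background is h = .43. If .46 is the effect detectable with 80% power at two-sided 5%, on the same scale (an assumption), power at .43 is F(2.802 × .43/.46 − 1.96) = F(.66), about 74-75%. H1A would then fail roughly one time in four at the pilot effect.

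**The case against.** Four points on the other side carry weight.

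- The error rates depend on an any-one-wins reading. The protocol does not state that rule. If all three endpoints had to be significant, no adjustment would be needed. But no such rule is stated either, and the absence of a decision rule is part of the finding.
- A reader might infer a chance of up to 19% of falsely declaring STEP effective. The documents do not support that. The figure counts errors in both directions, although the hypotheses are directional. It needs four independent tests, although two of them concern suicidal events in the same adolescents and active ideation comes from the same C-SSRS interview. It also treats the 12-month endpoint as primary, against Section 3 and Overall Design.
- A reader might infer that Section 8.1 already names suicidal events as the sole primary outcome, through "with the 6-month follow-up as our primary outcome (Ho1A". That sentence sits in the paragraph on suicidal events and may only select the time point for that measure. If it did name a sole primary outcome, the primary family would have one member and the inflation above would not arise. It makes H1A a natural first step but does not settle the hierarchy.
- A reader might extend the calculation to Aim 2. Those hypotheses belong to the secondary objective, and related affect measures in the same participants are not independent, so a combined error rate built on independence would mean little.

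None of this rescues the stated justification. Pre-specification is the only reason given, and it is not a valid one.

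**Conclusion.** The concern holds in a bounded form. With three 6-month primary endpoints, the plan as written carries about a 12.5-14% chance of at least one false positive for correlations of 0 to .5, falling to about 8% at .9. False claims of STEP benefit are about 6-7% for correlations of 0 to .5, roughly two and a half to three times the 2.5% of a single test. If 12-month suicidal events are also primary, the figures over the same correlations are about 16-19% and 8-10%.

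These sizes rest on two-sided 5% per test, on success being claimed from any one endpoint, and on the stated range of correlations. They take exactly one test per hypothesis; the open choices in H1B and the BDI-II informant could add tests. The contradictory label of the 12-month endpoint is a separate defect, and it leaves the size of the primary family unsettled.

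**What to change.** Delete the pre-specification justification and state a familywise procedure for the 6-month primary endpoints. Either of two would serve:

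- *Fixed sequence starting with H1A*, then H1B and H1C in a stated order, each at the full level, stopping confirmatory claims at the first non-significant step. H1A keeps its alpha, power and sample size. The cost is that H1B and H1C lose confirmatory status if H1A fails, roughly one time in four at the pilot effect under the assumption above.
- *Holm across H1A-H1C.* No endpoint blocks the others. The cost is some power on each; in the worst case an 80%-power test falls to about 66%.

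Print the significance level. So that the family is defined, fix one H1B outcome (worst-week binary or proportion of weeks) and one BDI-II informant. Label 12-month suicidal events secondary throughout, correcting the Synopsis, and reconcile Overall Design on which outcomes are assessed at 12 months. Label Aim 2 tests as supportive.

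These are wording changes to the protocol and any analysis plan. They need no extra participants or assessments, beyond accepting the power or claim restrictions just described.

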## Schedule of Activities

| **TABLE OF ASSESSMENTS** |  |  |  |  |  |  |
| --- | --- | --- | --- | --- | --- | --- |
| **Instrument** | **Admin to:** | **Type** | **Base** | **3M** | **6M** | **12M** |
| **Demographics** | A, G | Interview | X |  |  |  |
| **Suicidal and Self-Harm Behaviors:** |  |  |  |  |  |  |
| Columbia Suicide Severity Rating Scale (C-SSRS) | A, G | Interview | X | X | X | X |
| Suicide Ideation Questionnaire (SIQ) | A | SR | X | X | X |  |
| Suicidal Ideation Psychiatric Rating Scale – Longitudinal Follow-up Evaluation (LIFE-SI-PSR) | A | Interview | X | X | X |  |
| Functional Assessment of Self-Mutilation (FASM) | A | SR | X | X | X |  |
| **Diagnostic / Symptom Rating Scales:** |  |  |  |  |  |  |
| Beck Depression Inventory (BDI-II) | A, G | SR | X | X | X |  |
| Alcohol Use Disorder Identification Test (AUDIT) | A, G | SR | X | X | X |  |
| Drug Use Disorder Identification Test (DUDIT) | A, G | SR | X | X | X |  |
| Borderline Evaluation of Severity Over Time (BEST) | A, G | SR | X | X | X |  |
| Columbia Impairment Scale (CIS) | A, G | SR | X | X | X |  |
| **Treatment Targets of STEP:** |  |  |  |  |  |  |
| Attention Dot Probe Positive and Negative Stimuli | A | Task | X | X | X |  |
| Implicit Positive and Negative Affect Test | A | Task | X | X | X |  |
| Modified Differential Emotions Scale (mDES) | A | SR | X | X | X |  |
| Satisfaction with Life Scale (SWLS) | A | SR | X | X | X |  |
| Gratitude Questionnaire (GQ-6) | A | SR | X | X | X |  |
| **Ancillary Treatment Received:** |  |  |  |  |  |  |
| Treatment History Interview | A, G | Interview | X | X | X |  |
| Medication Compliance Questionnaire | A, G | Interview | X | X | X |  |
| **Implementation:** |  |  |  |  |  |  |
| Client Satisfaction Questionnaire | A, G | SR |  | A, G |  |  |
| Acceptability of Intervention Measure (AIM) | A, G | SR |  | A,G |  |  |
| Intervention Appropriateness Measure (IAM) | A, G | SR |  | A,G |  |  |
| Feasibility of Intervention Measure (FIM) | A, G, P (at different timepoints) | SR | P | A, G |  | P |
| Qualitative Exit Interviews | A, G, P (at different timepoints) | Interview | P | A, G |  | P |
| Evidenced Based Practice Attitude Scale (EBPAS) | P | SR | P |  |  | P |
| Implementation Climate Scale | P | SR | P |  |  | P |
| Implementation Readiness Scale | P | SR | P |  |  | P |

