## Measures to Minimize Bias: Randomization and Blinding

Eligible individuals who consent to participate will be randomly assigned to either STEP or ETAU. Co-I [name] will prepare a stratified (by study site, history of SB, and sexual or gender minority) randomization schedule using random blocks and provide this to our REDCap administrator; study staff will not have access to randomization tables). Research staff will be able to obtain assignments in real time once consent and stratification variable information are recorded. We use random block sizes to prevent guessing of pending treatment assignments. We stratify on history of past SB, because this factor has been shown to be a very strong predictor of a repeat hospitalization (6) and sexual or gender minority because this group is five times more likely to make a suicide attempt compared to heterosexual youth (51).

The assessment battery will be administered at baseline (prior to randomization) by the clinical interventionist. At the end of the active phase (3 months post-baseline), and at the 6- and 12-month follow-up intervals, assessments will be conducted by a blind evaluator, a research assistant located at a different site. For example, if the baseline assessment and sessions are conducted by the clinical staff at Butler Hospital or Bradley Hospital, the f/u assessments will be conducted by the Brown-based RA in another nearby building. Similarly, if baseline assessments and sessions are conducted by the clinical staff at BCH, the f/u assessments will be conducted by a Beth Israel Deaconess Medical Center (BIDMC) RA in another nearby building. The physical proximity of our sites (Brown to Butler/Bradley, and BIDMC to BCH) makes our plan to ensure blindness feasible.

In the event of inadvertent unblinding, the follow-up assessments will be conducted by another Research Assistant.

*6.4.* Study Intervention/Experimental Manipulation Adherence

Study intervention adherence will be tracked by the clinician via a clinician dashboard in REDCap. There will be tracking of attendance for in-person sessions, as well as tracking on whether there were any compressed sessions. Remote delivery adherence will be tracked based on the number of times the participant engages with the text messaging program, completion of the mood monitoring questions, and their response to the question of whether they have practiced the positive affect skill from the previous day.

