**Aim 1A-C:** *Examine the effectiveness of STEP in reducing suicidal events, active SI*, *and depression at 3- and 6-month follow-up (f/u).* We hypothesize that those randomized to STEP, compared to ETAU, will have (**H1A**) lower prevalence of suicidal events (operationalized as either a suicide attempt or emergency intervention to intercede when there is a high likelihood of an attempt) **(H1B**) lower prevalence of time with active SI (operationalized as SI with intent or plan), and (**H1C**) lower level of depressive symptoms, over the 6-month follow-up period. Aim 1 analyses will use a repeated measures design and a multilevel or mixed effect modeling framework. For H1A and H1B, the outcome is binary and a mixed effect logistic regression model will be used. For H1C, the outcome is continuous and a mixed effect general linear model will be used. For H1B, the outcomes are repeatedly observed over follow-up weeks within the 6M timeframe (24 weeks), and can yield a categorical (active SI, worst week) outcome, which would be analyzed like H1A or a continuous (proportion of weeks with active SI) outcome, which would be analyzed differently like H1C. For H1A and H1C the outcome is observed twice at the scheduled follow-ups (3M, 6M). For all hypotheses, we will treat the individual as the random effect. Treatment effects will be estimated as the weighted average of the differences between ETAU and STEP groups over all follow-up times, adjusting for follow-up time.

In secondary analyses to identify potential mechanisms (i.e. mediators) of treatment effectiveness that occur after randomization, we will repeat these analyses using medication use and psychosocial treatment as covariates.

In secondary analyses, payor data will be examined as a potential moderator or predictor of these outcomes.

In secondary analyses, the patterns of change in depressed mood (BDI scores) will be evaluated using random effects models for longitudinal data.

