**Aim 2:** *Examine engagement of the hypothesized mechanisms at the 3- and 6-month f/u.* We hypothesize that those randomized to STEP, compared to ETAU, will have*:* **H2A:** higher attention to positive affect, assessed by implicit tasks; **H2B**: Increased gratitude and satisfaction with life, assessed by self-report; **H2C**: lower attention to negative affect, assessed by implicit tasks and self-report. Aim 2 analyses will use a repeated measures design and a multilevel or mixed effect modeling framework. For H2A, H2B, and H2C, the outcomes are continuous and a mixed effect general linear model will be used. Outcomes are repeatedly observed over follow-up and assessed at the scheduled follow-up (3M, 6M). For all hypotheses, we will treat the individual as the random effect. Treatment effects will be estimated as the weighted average of the differences between ETAU and STEP groups overall follow-up times, adjusting for follow-up time. ***Sample size and statistical power considerations***: As with H1, we determined minimal detectable effect sizes using Monte Carlo methods. This involved generating 1,001 simulated data sets representing our hypothesized effects, and our assumptions of a 10% loss by 3M and another 10% loss by 6M follow-up. We assumed repeated measures of the measures assessing the mechanisms (attention to positive affect, gratitude and satisfaction with life, and attention to negative affect) to have a stronger correlation within a respondent over time than the Aim 1 outcomes, and assumed *r* = .75, which results in a smaller effective sample size. Across the simulated data sets, we compute power as the proportion of replicates returning a significant effect in the hypothesized direction. Results of these models are summarized in Table 3, above. We summarize effects in terms of Cohen’s effect size statistics for clear expression of the minimum detectable effects. For Aim 2 outcomes, we will have sufficient power to detect small-to-medium effect sizes (*d* = .39).

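### The Aim 1 and Aim 2 models name neither the baseline value nor the randomization strata as covariates, giving up precision that costs nothing to recover

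*Protocol*

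**What the plan says.** **Models (Section 9).** For Aim 1A-C the person is the random effect, and the treatment effect is the "weighted average of the differences between ETAU and STEP groups over all follow-up times, adjusting for follow-up time". On the responses: "For H1A and H1C the outcome is observed twice at the scheduled follow-ups (3M, 6M". H1B is observed weekly over 24 weeks. Aim 2 uses 3M and 6M outcomes and near-identical wording: "weighted average of the differences between ETAU and STEP groups overall follow-up times, adjusting for follow-up time". Aim 1D is a separate logistic regression at 12 months, with no covariate named.

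**Covariates named elsewhere in Section 9.** Medication use and psychosocial treatment, both arising after randomization, enter secondary analyses, and payor is examined as a moderator or predictor. Baseline data serve to compare completers with dropouts and to check balance between arms.

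**What is known before randomization.** Section 6.3 describes a "stratified (by study site, history of SB, and sexual or gender minority) randomization schedule using random blocks" and explains: "We stratify on history of past SB, because this factor has been shown to be a very strong predictor of a repeat hospitalization". Section 9 adds: "Our randomization procedures include stratification on important predictors of the main outcome variable". The Schedule of Activities (Section 1.3) lists "Beck Depression Inventory (BDI-II) | A, G | SR | X | X | X", that is, baseline, 3M and 6M. The C-SSRS and the Aim 2 measures also have a baseline mark.

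**The concern.** The design restricts randomization on factors that the protocol considers prognostic and measures each continuous outcome before assignment. The stated models then use none of this. Two things follow.

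For a continuous outcome, variance that the baseline value could explain stays in the error term, so H1C (a primary outcome) and all of Aim 2 (target engagement, on which the Aim 3 mediation analysis depends) are less precise than the data allow.

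For a binary outcome, stratified allocation makes the arms more alike on prognostic factors than simple randomization would. A model that leaves the strata out does not credit that balance, so its standard error is too large and its test rejects too rarely.

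There is also a practical point. Section 9 plans to look at baseline differences between arms. If no covariate set is fixed first, any adjustment prompted by that look would be post hoc.

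**Working it through.** **1. Inputs.** From the protocol: 216 participants, 1:1, so 108 per arm; 10% lost by 3M and another 10% by 6M, so per arm 86.4 have both visits and 10.8 have 3M only; within-person correlation r = .5 (Aim 1) and .75 (Aim 2); stated detectable effects .35 (H1C) and .39 (Aim 2). Assumed: two-sided alpha .05 and 80% power, so the multiplier is 1.960 + 0.842 = 2.802. Section 9 speaks only of sufficient power for these aims.

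**2. Reproducing the stated figures without covariates.** For a common effect over two visits with compound symmetry:

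- Information per arm = 108 × [0.8 × 2/(1 + r) + 0.1]; SE = √(2/information); detectable effect = 2.802 × SE.
- H1C: 108 × (1.6/1.5 + 0.1) = 126.0; SE .126; effect .353, against .35 stated.
- Aim 2: 108 × (1.6/1.75 + 0.1) = 109.5; SE .135; effect .379, against .39 stated. Power at .39 is 82%, so the match is close but not exact.

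**3. Adding the baseline value.** If baseline correlates b with each follow-up, the residual variance is 1 − b² and the residual correlation is (r − b²)/(1 − b²). Information per arm becomes 108 × [1.6/(1 + r − 2b²) + 0.1/(1 − b²)].

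| Outcome | r | b | Information | SE | Detectable effect |
|---|---|---|---|---|---|
| H1C | .5 | none | 126.0 | .126 | .353 |
| H1C | .5 | .3 | 142.8 | .118 | .332 |
| H1C | .5 | .5 | 187.2 | .103 | .290 |
| Aim 2 | .75 | none | 109.5 | .135 | .379 |
| Aim 2 | .75 | .3 | 121.9 | .128 | .359 |
| Aim 2 | .75 | .75 | 301.2 | .081 | .228 |

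At b = .5 the H1C gain equals 187.2/126.0 = 1.49 times the sample, and power at d = .35 goes from 79% to 92%. At b = .3 it equals 142.8/126.0 = 1.13 times.

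**4. Do the stated effects show which model was powered?** Changing the power level in the same formula gives, for H1C and Aim 2:

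- no baseline, 80% power: .353 and .379;
- b = .3, 85% power: .355 and .384;
- b = .45, 90% power: .350 and .385.

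All three are compatible with .35 and .39, so the stated effects do not settle it.

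**5. Binary outcomes, by simulation.** Stratified random blocks; 216 randomized. Single-time logistic regression: about 162 analyzed, 6,000 runs per cell; history of suicidal behavior and minority status each at 52% prevalence (pilot shares) with the stated odds ratio; three sites (50/25/25) with no effect on outcome; rates near 38% and 17% when the strata carry no effect. Mixed logistic: random-intercept SD 1.8 (assumed), 2,500 null and 1,000 alternative runs.

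| Model | Stratum OR | Alpha, strata out / in | Power, strata out / in | Power lost (points) |
|---|---|---|---|---|
| Logistic | 1 | 5.4% / 5.7% | 84.6% / 84.9% | 0.3 |
| Logistic | 2 | 4.1% / 4.9% | 83.5% / 85.2% | 1.7 |
| Logistic | 3 | 3.8% / 4.9% | 79.5% / 83.2% | 3.7 |
| Logistic | 5 | 3.2% / 5.1% | 73.5% / 80.7% | 7.3 |
| Mixed | 2 | 4.8% / 5.3% | 84.1% / 85.6% | 1.5 |
| Mixed | 5 | 3.1% / 5.2% | 79.1% / 84.2% | 5.1 |

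Simulation error is about 0.3 points for logistic alpha, 0.4 for mixed-model alpha and 1.2 for mixed-model power. Compare within rows only: the conditional effect is held fixed, so the marginal difference shrinks as the stratum odds ratio grows.

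**The case against.** **The covariate list may sit in a separate SAP.** This is a fair point. The sentence on follow-up time explains how visit differences are averaged; it does not say that nothing else may enter. Section 9 also allows modification after review. Even so, Section 9 presents its text as the pre-specification, states the estimator, and names covariates where it wants them. Improving a stated model is a legitimate comment, but it does not show that adjustment is forbidden.

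**A reader might infer from .35 and .39 that baseline was excluded.** The figures do not support that (step 4). In any case, omitting covariates from a power calculation is a common simplification and does not fix the analysis model.

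**A reader might take the protocol to call all the strata very strong predictors.** It says this of history of suicidal behavior only, and for repeat hospitalization. Section 9 calls the strata, collectively, important predictors of the main outcome. The five-fold attempt risk cited for minority youth is a comparison with heterosexual youth, not a figure for suicidal inpatients. Site is given no prognostic rationale. Odds ratios of 2 to 5 are therefore assumptions.

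**The larger gains are a favorable case.** They need baseline to correlate with follow-up as strongly as the follow-ups do with each other. Baseline is taken during a crisis admission, so a lower value is plausible and the gain could be modest. This stands, and it is why ranges are given.

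**The unadjusted comparison is valid.** This stands as well.

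**Conclusion.** The point holds as a matter of efficiency. As stated, the Aim 1 and Aim 2 models leave out prognostic information that is in hand at randomization. Under the assumptions above, adjustment improves the detectable effect by about .02 to .06 for H1C and about .02 to .15 for Aim 2.

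For the binary outcomes, a reader might infer that the false-positive rate is inflated. The opposite is true: where the strata are prognostic the tests run below 5%, and the harm is lost power. If the strata are not prognostic, there is essentially no effect. Nor does this undermine the planned 216, since the unadjusted calculation already comes close to the stated effects at 80% power.

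The baseline argument does not extend to H1A. Every participant is admitted for suicide risk, so baseline event status is nearly constant; there the useful covariates are the strata.

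**What to change.** In Section 9, state that:

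- every Aim 1A-D and Aim 2 model includes site, history of suicidal behavior and sexual or gender minority status as fixed effects, coded as used in the randomization. The synopsis lists three sites but the recruitment section counts two clinical sites, so give the number of levels;
- the H1C model and all Aim 2 models also include the baseline value of the outcome;
- baseline ideation severity is optional for H1B;
- because covariate adjustment changes what the odds ratio means, a covariate-standardized risk difference is reported beside it for each binary outcome.

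Main effects are enough: three site levels and two binary factors add four terms. At the H1D rates, 81 × (.38 + .17) gives about 45 events to support them.

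The cost is wording and routine analysis code, to be settled before arm-level outcome data are seen. All the covariates are recorded before assignment, so no new data, visit or participant is needed.
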